### Analytic strategy

To achieve the three main objectives of this study, several retrospective and forecasting methods will be integrated. The detailed steps of each objective are described below. As discussed before, the Aim 1 is to use very large datasets to evaluate the effect of a broad range of socioeconomic determinants on incidence, treatment adherence, hospitalization, case fatality and mortality from HIV/AIDS. A hierarchical framework to investigate the social determinants of HIV/AIDS [40, 48] will be developed. Social indicators will be grouped into three blocks representing distal, intermediate, and proximal variables. Distal variables are related to geographical factors and include region and location of the family household (urban or rural). Intermediate variables are related to socioeconomic position in the community and include self-identified race or ethnicity, education, employment, and *per capita* family income. Proximal variables are related to household conditions at the family level and include building material, water supply, sanitation, electricity, waste disposal destination, and household density. Following a hierarchical analytical approach, three adjusted Poisson regression models will be used with cluster-robust standard errors (SEs) [49–51], i.e., accounting for familial clustering of covariates, to estimate the adjusted incidence rate ratios (IRRs) of morbidity or mortality HIV/AIDS outcomes. All variables associated with Incidence Rate Ratio of the outcomes at a significance threshold of p-value less than 0.10 will be included in the next level model. Model 1 will include distal factors plus age and sex. Model 2 will include variables from model 1 and intermediated factors. Model 3 will include variables from model 2 and proximal factors.

The second aim of this study is to assess the impact of the Bolsa Familia Program exposure and Primary Health Care coverage on incidence, treatment adherence, hospitalization, case fatality, and mortality from HIV/AIDS, evaluating their impact, alone and in a synergistic fashion, on a broad range of subpopulations. To achieve this goal, the following steps will be performed:

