**Step 1**. To analyze the differential impact and dose-response of BFP according to the duration of the intervention, amount of money received and compliance with conditionalities. The retrospective impact evaluation will use arguably one of the most robust study designs for causal inference in quasi-experimental studies: the regression discontinuity design (RDD), which allows a quasi-randomization of the subjects under study around the eligibility threshold [52, 53]. The eligibility of the BFP is determined by two thresholds: one for poor families (below 154 BRL *per capita*) with vulnerable members (children or pregnant women), the second for extremely poor families (below 77 BRL *per capita*), even without any vulnerable member. BFP is one of the most accurately targeted CCTs, and if inclusion/exclusion errors are identified, a fuzzy-instead of sharp-RDD will be used. The presence of two different cut-offs will allow to evaluate the different impact of the BFP on the two different thresholds: between eligible and non-eligible poor and eligible and non-eligible extremely poor families. In order to explore the impact in subjects outside of the RDD selected bandwidth, analyses using Random Administrative Delays (RAD) and Propensity Score Matching (PSM) [54–56] will also performed. These methods have been already used for similar studies with the CadUnico to evaluate the effects of BFP on Tuberculosis (TB). The PSM has also been used in with the same linked dataset to complementarily evaluate the impact of BFP on TB cure and mortality rate [21]. Where possible, combination of these designs—such as the PSM-RDD—will be used [57]. The complementary use of the three methods will consequently allow to assess the effects of BFP along the complete range of socioeconomic conditions represented over the 100 million individuals of the dataset. All analyses above will be stratified according to the years of exposure to BFP and amount of received money over the 12 years of follow-up, to evaluate a dose-response relation with the duration and intensity of support received. Analyses will also explore lagged effects by associating exposures of previous years with outcomes of a range of following years.**Step 2**. To measure the BFP impact on a broad and detailed range of different subpopulations defined by individual demographic and socioeconomic characteristics and by local geographic regions, and municipality development. The evaluation designs and methods described above will be used for stratified analyses with each subpopulation of interest: age groups, gender, illiteracy and educational level. Further stratifications will be based on the characteristics of the municipality: human development index, GDP per capita and Gini index of income inequality.**Step 3**. To analyze the dose-response of FHS according to the extent and duration of the municipal coverage. Using the same structured dataset from the previous analyses of Aim 2, and considering that coverage of FHS is only available at the municipal level, the FHS impact will be evaluated using a Propensity Score (PS) weighted multilevel negative binomial regression design with individual level-variables from Aim 1, including BFP as adjusting variable [56]. To avoid ecologic fallacy, the dataset will be resized and limited to municipalities with 90–100% (consolidated FHS coverage = exposed) and 0–10% FHS coverage (low/insignificant FHS coverage = control) in the study period. The intervals 0–10% and 90–100%, instead of 0% and 100%, will be used to consider uncertainty in the coverage measure, but sensitivity analyses will be performed with 0% and 100%.**Step 4**. To measure the FHS impact on a broad range of different subpopulations defined by individual demographic and socioeconomic characteristics and by local geographic regions. As in the Step 2 of the Aim 2, the evaluation designs and methods will be used for each subpopulations of interest: age groups, gender, illiteracy and educational level. Moreover, further stratifications also will be based on the characteristics of the municipality.**Step 5**. To evaluate the synergistic individual-level exposure to BFP with municipal-level coverage of FHS on incidence and mortality from HIV/AIDS. Using the same multilevel and multivariable regression models above, the interaction effects of BFP with FHS will be evaluated with product terms and stratification analyses.

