Scenarios will be compared along ratios of HIV/AIDS incidence, prevalence and mortality, and the number of averted cases and deaths. The main potential limitation of our comprehensive MS-CM-ABM models is that they are built upon effect estimates coming from the poorest half of the Brazilian population, while our models will forecast the entire HIV/AIDS burden of the country. As mentioned above, the inputs for modelling will be integrated with parameters from nationally representative studies and there are solid reasons why we assume FHS and BFP effects obtained in Aim 1 and Aim 2 represent the impact on the overall Brazilian population. We will use R Studio^®^ 3.6 and JAS-mine^®^ [71] for MS, CM and ABM and their integration in Aim 3.

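### Aim 2 Step 5 does not fix the scale of BFP–FHS synergy, and its product terms can give the opposite answer from synergy in cases averted

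*Protocol article*

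**What the plan says.** In the protocol article, Analytic strategy, Aim 2, the goal of Step 5 is "To evaluate the synergistic individual-level exposure to BFP with municipal-level coverage of FHS on incidence and mortality from HIV/AIDS". The method is given in one sentence, which says that "the interaction effects of BFP with FHS will be evaluated with product terms and stratification analyses". For the models it only points back to earlier steps: "Using the same multilevel and multivariable regression models above".

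The models referred to are those of the preceding steps. Step 3 specifies a "Propensity Score (PS) weighted multilevel negative binomial regression design with individual level-variables from Aim 1, including BFP as adjusting variable". It compares municipalities with 90–100% FHS coverage against those with 0–10%. The related Poisson models of Aim 1 are used "to estimate the adjusted incidence rate ratios (IRRs) of morbidity or mortality HIV/AIDS outcomes".

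Aim 3 takes its parameters from Aims 1 and 2. Its outcome comparison is stated as follows: "Scenarios will be compared along ratios of HIV/AIDS incidence, prevalence and mortality, and the number of averted cases and deaths".

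The article does not say whether synergy means departure from additive or from multiplicative effects. It names no additive interaction measure and gives no rule for concluding that synergy is present.

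**The concern.** A product term in a log-link count model is a ratio of rate ratios. It equals 1 when the two effects multiply. Synergy in cases or deaths prevented is a different question: do the two programs together avert more than the sum of what each averts alone? For two protective exposures the two scales disagree over a whole range of results, and in that range a product term below 1 looks like extra protection although the joint program averts less than the sum.

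The choice matters here because the joint effect of cash transfer and primary care is a named part of Aim 2 and is presented as one of the study's innovations. Aim 3 then compares combined expansions of both programs and reports averted cases and deaths, which are additive quantities. A reader could meet a ratio-scale finding of synergy in Aim 2 next to Aim 3 results in which joint expansion averts less than the sum of the parts, with nothing in the plan to explain the difference.

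**Working it through.** The article gives no effect size, event count, alpha or power for the interaction, so there is no stated figure to reproduce. The check is algebra, with assumed rate ratios.

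**Inputs.** b is the rate ratio for BFP alone and f the rate ratio for FHS alone, each against neither program. All values are assumed. FHS is binary through Step 3's coverage bands; BFP is taken as yes/no. The log link is inferred from the model type and the incidence rate ratios.

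**Formulas.**
- Joint rate ratio under exact additivity: b + f − 1.
- Joint rate ratio under exact multiplicativity: b × f.
- Product term when the truth is additive: (b + f − 1)/(b f) = 1 − (1 − b)(1 − f)/(b f). This is below 1 whenever both b and f are below 1.
- Relative excess risk due to interaction (RERI) = joint − b − f + 1. When the truth is multiplicative this is (1 − b)(1 − f), above 0 for two protective programs. A positive value means a joint rate higher than additivity predicts, so fewer cases averted.

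| b, f | Additive joint | Multiplicative joint | Product term if additive | RERI if multiplicative |
|---|---|---|---|---|
| 0.95, 0.95 | 0.90 | 0.9025 | 0.997 | +0.0025 |
| 0.9, 0.9 | 0.80 | 0.81 | 0.988 | +0.01 |
| 0.8, 0.8 | 0.60 | 0.64 | 0.938 | +0.04 |
| 0.8, 0.7 | 0.50 | 0.56 | 0.893 | +0.06 |
| 0.7, 0.6 | 0.30 | 0.42 | 0.714 | +0.12 |
| 1.2, 0.8 (one harmful) | 1.00 | 0.96 | 1.042 | −0.04 |

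**The range of disagreement, for 0.8 and 0.7.** The separate effects avert 0.20 + 0.30 = 0.50 of the baseline rate.
- Product term 1: joint 0.56, averted 0.44, which is 0.06/0.50 = 12% fewer than the sum. At an assumed baseline of 20 per 100,000 this is 20 × 0.44 = 8.8 averted against 20 × 0.50 = 10.0.
- Product term 0.95: joint 0.95 × 0.56 = 0.532, averted 0.468. This is still fewer than the sum, yet on the ratio scale it looks like synergy.
- Product term 0.893: joint 0.50, exactly additive.

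Only below 0.893 do both scales point to synergy.

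**Would the departure be significant?** This is the chance of a significant product term below 1 when the truth is exactly additive. It uses a two-sided 5% Wald test with SE = √(sum of 1/events over the four cells), equal person-time per cell, and events divided by the design effect (DE). Event totals and DE are assumed.

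| b, f | Events | DE 1 | DE 5 |
|---|---|---|---|
| 0.9, 0.9 | 1,000 | 3% | 3% |
| 0.9, 0.9 | 100,000 | 16% | 6% |
| 0.8, 0.7 | 1,000 | 14% | 6% |
| 0.8, 0.7 | 5,000 | 49% | 14% |
| 0.8, 0.7 | 20,000 | 97% | 41% |
| 0.8, 0.7 | 100,000 | 100% | 97% |

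The consequence runs from negligible to decisive, depending on effect sizes, events and clustering.

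**The case against.** The strongest reply is that the multiplicative scale is a legitimate estimand, that the article nowhere defines synergy as extra cases averted, and that an additive measure is reporting detail which a full analysis plan may add. Part of this stands. The product term is not an error, and whether a fuller plan supplies an additive contrast cannot be seen from the article. But the article does fix a method for a named aim, and that method can answer the synergy question in the opposite direction from the averted-case scale that the same study reports.

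Four stronger readings are tempting and are not supported:

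- *Product terms are the only tool.* Step 5 also plans stratification. Stratum-specific rates or rate differences would show the additive picture. Stratum-specific rate ratios from the same models would not, and the article does not say which will be reported.
- *Merely additive programs will be declared synergistic.* The article says that interaction will be evaluated. It states no threshold or decision rule.
- *Aim 3's averted counts will be on the wrong scale.* Aim 3 compares ratios as well as "the number of averted cases and deaths". With two binary exposures, both main effects and the product term give all four cell rates, so a simulation that carries them all obtains averted cases correctly.
- *The cohort is so large that any departure will be significant.* No event count is given for this analysis, FHS varies only by municipality, and Step 3 restricts the municipalities used. For 0.9 and 0.9 the chance is 16% even at 100,000 events without clustering.

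**Conclusion.** The point holds as a gap in definition: Step 5 names synergy as its target, offers ratio-scale tools, and leaves the scale open. For two protective programs, a product term between (b + f − 1)/(b f) and 1 suggests synergy on the ratio scale while fewer cases are averted jointly than the sum of the two. The width of that range depends on the effects: it starts at 0.988 for 0.9 and 0.9, at 0.893 for 0.8 and 0.7, and at 0.714 for 0.7 and 0.6. It is negligible if both effects are weak.

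This rests on the inferred log link, on assumed rate ratios, and on both programs being protective. If one is harmful, exact additivity gives a product term above 1 instead. Statistical significance cannot be judged without event counts and the degree of municipal clustering. It is worth correcting because the remedy comes from the same fit.

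**What to change.** In Aim 2 Step 5, state the scale on which synergy is claimed. Beside the product term, report an additive-interaction contrast from the same weighted model: either RERI, or standardized rates for the four BFP × FHS cells with their interaction contrast. Give it a confidence interval clustered by municipality. State the sign convention, since with protective exposures a negative RERI is the direction of extra cases averted. Base any statement about synergy in cases or deaths averted on this contrast. The product term can stay as a reported measure of multiplicative interaction; there is no need to demote it.

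In Aim 3, carry the joint four-cell effects, including the product term, into the scenarios that expand both programs.

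The cost is a little post-estimation work. No new data and no change of model are needed.

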**Fig 3 pone.0265253.g003:**
[figure not shown]
Integrated microsimulation, compartmental and agent-based model.

For each outcome and each scenario, 10,000 Monte Carlo simulations will be performed allowing all parameters to vary by their underlying distribution—measured in the retrospective analysis—and consequently obtaining the Predictive Intervals of each estimate. The linear regression of predicted versus observed values and the proportion of variance (R^2^) explained will be assessed, and will be verified that all observed values will be included in the 95% CIs of the simulation estimates, among other validation criteria [69, 70].

Once the MS-CM-ABM models are validated, we will use them to:
Forecast the prolonged effects of the ongoing increases in poverty rates due to the economic crisis and the impact of reductions in BFP and FHS coverages due to the currently implemented fiscal austerity measures, versus different dynamics of improved socioeconomic scenarios and stabilization or increases in BFP and FHS coverage up to 2030.Evaluate in which specific subpopulation groups increased BFP and FHS coverage could be more beneficial. Using the granularity of MS-ABM and subpopulation specific effect estimates from the retrospective evaluation several scenarios of expansion of BFP and FHS in target populations will be tested, and the benefits compared.Evaluate with comprehensive calibration which combination of socioeconomic determinants changes and BFP and FHS subpopulations coverage will allow to reach AIDS-related Sustainable Development Goal 3.3 in Brazil. Using the comprehensive set of scenarios evaluated above, the combinations of socioeconomic changes and interventions expansions will be more finely tuned to maximize the chances to reach the end of HIV/AIDS epidemic in Brazil.

Scenarios will be compared along ratios of HIV/AIDS incidence, prevalence and mortality, and the number of averted cases and deaths. The main potential limitation of our comprehensive MS-CM-ABM models is that they are built upon effect estimates coming from the poorest half of the Brazilian population, while our models will forecast the entire HIV/AIDS burden of the country. As mentioned above, the inputs for modelling will be integrated with parameters from nationally representative studies and there are solid reasons why we assume FHS and BFP effects obtained in Aim 1 and Aim 2 represent the impact on the overall Brazilian population. We will use R Studio^®^ 3.6 and JAS-mine^®^ [71] for MS, CM and ABM and their integration in Aim 3.

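### The Aim 3 validation rule asks 95% intervals to contain every observed value: it can reject a correct model, and it gets easier to meet as the intervals widen

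*Protocol article*

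**What the plan says.** The rule is in the Protocol article, Analytic strategy, Aim 3, in the text after Fig 3. For each outcome and scenario there are 10,000 Monte Carlo runs, "allowing all parameters to vary by their underlying distribution", with those distributions coming from the retrospective analysis and "consequently obtaining the Predictive Intervals of each estimate". Validation is then described in one sentence. "The linear regression of predicted versus observed values and the proportion of variance (R^2^) explained will be assessed", and it "will be verified that all observed values will be included in the 95% CIs of the simulation estimates". Further validation criteria are mentioned by citation but not named.

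Validation is the condition for everything that follows: "Once the MS-CM-ABM models are validated, we will use them to" introduces the austerity and recovery scenarios to 2030, the choice of subpopulations for expanded coverage, and the search for combinations that reach SDG 3.3.

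The text gives no number of observed values to be checked, no limit on interval width, and no target for slope, intercept or R-squared. The interval is called predictive in one sentence and a CI in the next.

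**The concern.** A 95% predictive interval that behaves as designed leaves about one value in twenty outside. A rule that allows none outside counts this expected behaviour as a failure. It also acts in one direction only: widening the intervals always makes it easier to meet, and nothing in the stated criteria counts against width. The one summary named from the regression, R-squared, does not change when all predictions are shifted or rescaled.

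All Aim 3 conclusions are at stake, because they depend on the models having been validated. Applied literally, the rule could discard a sound model, or accept one whose intervals are too wide to separate the policy scenarios. The Aim 1 and Aim 2 estimates are not affected.

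**Working it through.** The article states no pass probability, so there is no figure to reproduce.

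**Inputs**
- Nominal coverage: 0.95 (validation sentence after Fig 3).
- Outcomes forecast: 3, namely incidence, prevalence and mortality (Aim 3).
- Years of data: 19 (Abstract, Methods and analysis). The Innovation section gives 18 years of follow-up and Aim 2 Step 1 gives 12.
- Number of values checked, n: not stated. *Assumption:* annual national values, so 19 for one outcome and 19 × 3 = 57 for three. The shortest case is 12 years of one outcome. Checking by subpopulation would raise n.

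**1. Correct model, independent errors.** P(all inside) = 0.95^n, and the expected number outside is 0.05 × n.

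| n | P(all inside) | Expected outside |
|---|---|---|
| 12 | 54% | 0.60 |
| 13 | 51% | 0.65 |
| 14 | 49% | 0.70 |
| 19 | 38% | 0.95 |
| 57 | 5% | 2.85 |

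Failure becomes more likely than not from n = 14, since ln 0.5 / ln 0.95 = 13.5.

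**2. Correct model, serially correlated errors.** Calibrated AR(1) errors over 19 years were simulated 40,000 times. The Monte Carlo standard error is at most √(0.25/40,000) = 0.25 percentage points.

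| Yearly correlation | One outcome | Three outcomes, uncorrelated | Three outcomes, cross-correlation 0.8 |
|---|---|---|---|
| 0.5 | 44% | 8% | 20% |
| 0.8 | 59% | 21% | 35% |
| 0.9 | 70% | 35% | 50% |
| 0.95 | 79% | 49% | 63% |

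**3. Effect of width and bias** (n = 57, independent errors; bias in units of the true predictive SD).
- Twice the correct width, no bias: passes 99.5%.
- Twice the correct width, bias 1 SD: passes 90%.
- Three times the correct width, bias 2 SD: passes 99.7%.
- Correct width, bias 1 SD: passes about 0%.

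For a correct model to pass 57 independent points with 95% probability, each interval must be at level 0.95^(1/57) = 0.9991. Then z = 3.32, and 3.32/1.96 = 1.69 times the width of a true 95% interval.

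**4. R-squared.** In an illustrative declining 19-year series, R-squared is 0.972 for unbiased predictions, for the same predictions multiplied by 1.5, and for the same predictions plus 5. The regression of observed on predicted does show the error. The slope moves from 1.03 to 0.69 under rescaling (1.03/1.5), and the intercept from −0.6 to −5.8 under the shift (−0.61 − 5 × 1.03).

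**5. Type of interval.** The only source of spread the text names is variation in the parameters. If outcome variation is left out, the intervals are too narrow for observed values. Their coverage falls below 95%, and the pass rates in steps 1 and 2 are then too favourable.

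**The case against.** Several stronger readings are tempting, and the document does not support them.

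- **A reader might infer that a correct model usually fails.** That depends on n and on the correlation of the errors, and the article gives neither. Independence is also an unlikely case: parameter errors are shared across years, and prevalence carries over from one year to the next. With one outcome and yearly correlation of 0.8 or more, a correct model passes more often than not. What stands is a substantial risk of rejection: 21% to 41% for one outcome at correlations of 0.95 to 0.8, and 37% to 79% for three.
- **A reader might infer that a biased model passes.** With correct width it almost always fails. Bias gets through only when the intervals are also too wide.
- **A reader might infer that validation rests on this rule and R-squared alone.** The article also plans the regression itself, which can expose bias, and cites further criteria. An article may leave their thresholds to a fuller document. That softens the point, but it does not correct a coverage rule that is stated outright.
- **A reader might infer that analysts would widen distributions in order to pass.** The text ties the distributions to the retrospective estimates and nowhere allows widening. The fair statement is that the rule does not penalise imprecision, whatever its source.
- **A reader might infer that the models are checked against the data that produced their parameters.** Overlap is likely, but the observed series is not identified, and the limitations paragraph for Aim 3 says inputs are supplemented from nationally representative studies.

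It can also be said that no sentence makes one value outside an automatic rejection. That is true, but the criterion as worded is unmet when a single value falls outside.

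**Conclusion.** The point holds in limited form. The coverage criterion is wrongly stated: it demands 100% from a nominal 95% interval, puts no limit on width, and forms part of the validation on which the forecasts depend.

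Its size cannot be fixed from the document. On the annual-national assumption, a correct model's pass rate is 38% (19 values) or 5% (57 values) with independent errors. At yearly correlations of 0.8 to 0.95 it rises to about 59–79% for one outcome and 21–63% for three. The opposite fault is clearer: at n = 57 with independent errors, doubling the interval width takes the pass rate from 5% to 99.5%. Neither a general failure of correct models nor a general acceptance of biased ones is established.

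**What to change.** 1. Replace the all-values requirement with the empirical coverage of the 95% predictive intervals, compared with the nominal 95%, and report it with interval width or an interval score. State which values are checked and how many. Because errors are likely to be correlated, judge the number of misses against its distribution across the simulated trajectories, not against simple binomial limits.
2. Judge the planned regression, fitted as observed on predicted, by intercept near 0 and slope near 1, not by R-squared alone.
3. Use predictive intervals that include outcome variation as well as parameter uncertainty, and use that term throughout in place of 95% CIs.

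Optional: a check on held-out late years, such as 2015–2018, would test forecasting more directly. It gives only 4 annual values per outcome, or 12 in all. A calibrated model would have all 12 inside with probability 0.95^12 = 54% under independence, so this cannot test coverage precisely. It also means re-estimating the inputs on shortened data.

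The core change costs slightly more reporting and gives up a simple pass/fail statement. The optional check costs more, for the re-estimation and the repeated simulations.

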### Innovation of the study

This study breaks new ground by providing a unique opportunity to use unprecedented big longitudinal dataset of linked socioeconomic and health data to assess the effects of socioeconomic conditions, PHC and CCT on all sequential outcomes of HIV/AIDS morbidity and mortality. Moreover, this study provides the unique opportunity to assess potential effect modification and synergistic effects of the simultaneous receipt of CCT and PHC, and how baseline socioeconomic conditions influence the effectiveness of both types of programs on the burden of HIV/AIDS. The longitudinal aspect of the cohort, which has a long follow-up period of 18 years of socioeconomic and health data, will allow us to explore and assess in-depth dynamics, lagged and long-term effects of changes in living conditions and in exposures to BFP and PHC. One of the study’s most relevant potential contribution to translational science will be the systematic integration of the large dataset and results from the retrospective impact evaluations with the prospective mathematical models, developing more reliable forecast scenarios than models which use parameters from other studies or populations. Moreover, the creation of a pioneering hybrid microsimulation, compartment and agent-based model (MS-CM-ABM), which will be supported by the very large number of parameters available from the retrospective big data evaluation, will be an innovation in the epidemiology of infectious diseases, and will be essential to the effort of modelling the effects of social determinants, CCT and PHC on HIV/AIDS. To date, very few studies in HIV/AIDS have introduced poverty and CCT as variables in their predictive models, and they have not explored their influence in depth [34, 35]. Regarding PHC, no models have assessed the impact of access to universal PHC on HIV/AIDS-relevant outcomes (beyond universal HIV screening in primary care settings) [36], neither have mathematical models been developed to estimate these effects.

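### Separately stratified effect estimates drive the targeting scenarios with no between-group heterogeneity estimate or pooling, so the best-looking group's relative effect may be overstated, mainly where events are sparse

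*Protocol article*

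**What the plan says.** All places are in the Protocol article.

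- **Analytic strategy, Aim 2 Step 2 (BFP).** "The evaluation designs and methods described above will be used for stratified analyses with each subpopulation of interest". The individual-level factors are age, gender, illiteracy and education. Municipal factors follow: "Further stratifications will be based on the characteristics of the municipality: human development index, GDP per capita and Gini index of income inequality".
- **Aim 2 Step 4 (FHS).** The same approach: "the evaluation designs and methods will be used for each subpopulations of interest: age groups, gender, illiteracy and educational level", with municipal strata added.
- **Aim 2 Step 5.** Product terms are specified for the interaction of BFP with FHS. None is specified for either programme by subpopulation.
- **Innovation of the study.** Effect modification is posed as a question, including "how baseline socioeconomic conditions influence the effectiveness of both types of programs on the burden of HIV/AIDS".
- **Aim 3, use of the validated models.** One task is: "Evaluate in which specific subpopulation groups increased BFP and FHS coverage could be more beneficial". For this the models take "subpopulation specific effect estimates from the retrospective evaluation several scenarios of expansion of BFP and FHS in target populations will be tested, and the benefits" compared. In a further task, "the combinations of socioeconomic changes and interventions expansions will be more finely tuned to maximize the chances to reach the end of HIV/AIDS epidemic".
- **Aim 3, uncertainty and scale.** Each outcome and scenario gets 10,000 Monte Carlo runs, with parameters drawn from distributions measured in the retrospective analysis. Scenarios are compared on ratios and on averted cases and deaths.

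**The concern.** The stated chain runs from separate stratum estimates, to a comparison of projected benefits, to tuning of combinations. No step described in it asks whether the programme effect differs between strata. Each stratum estimate is the true effect plus sampling error, so the group that looks best after a comparison tends to be one whose error was favourable. Its relative effect is then too strong on average, and that error passes into the averted cases and deaths projected for it.

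What is at stake is the advice on which groups should get expanded coverage, and on which mix could reach Sustainable Development Goal 3.3. The article also presents effect modification by baseline conditions as a question of its own, and a set of separate fits does not by itself answer that.

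**Working it through.** The article gives no event counts, power or effect size for the subgroup work, so there is no figure of its own to reproduce. The checks below rest on stated assumptions.

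**1. Size of the overstatement when all strata share one effect**

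From the article: seven named stratifiers (age, gender, illiteracy, education, municipal HDI, GDP per capita, Gini).

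Assumed: 5, 2, 2, 4, 3, 3 and 3 equal-sized levels, so 5+2+2+4+3+3+3 = 22 strata; one programme and one outcome; half the person-time exposed; true IRR 0.90 in every stratum. Poisson events are split at random into the levels of each factor. The lowest of the 22 estimated IRRs is recorded and averaged over at least 2,000 simulations per setting.

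Overstatement = (1 − lowest IRR) / (1 − 0.90).

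| Total events | Lowest IRR, mean | Overstatement |
|---|---|---|
| 1,000 | 0.73 | 0.27/0.10 = 2.7 |
| 5,000 | 0.82 | 0.18/0.10 = 1.8 |
| 20,000 | 0.86 | 0.14/0.10 = 1.4 |
| 100,000 | 0.88 | 0.12/0.10 = 1.2 |

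A rerun of this design for the present note gave 2.6, 1.8, 1.4 and 1.2. At 400,000 events the factor is about 1.09.

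**2. A second set of assumptions**

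Take K independent equal strata, true RR 0.85 in each, and SE of the log RR = √(4/events). With K = 10 and 1,000 events per stratum, SE = √(4/1000) = 0.063. The expected minimum of 10 standard normal values is about −1.54, so the lowest RR averages 0.85 × exp(−1.54 × 0.063) ≈ 0.77. The simulation gave 0.771 and a 1.52-fold overstatement. At 20,000 events per stratum the factor was 1.08 (K = 4), 1.12 (K = 10) and 1.15 (K = 20).

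**3. Whether the Monte Carlo step removes it**

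In the setting K = 10, 1,000 events per stratum and true RR 0.85, draws were centred on each stratum's own estimate (2,000 replicates of 2,000 draws). For the stratum with the lowest estimate:

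- the mean simulated RR was 0.773, still below 0.85;
- its 95% interval covered 0.85 in 77% of replicates;
- its simulated probability of being best averaged 44%, against 10% under exchangeability.

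The draws show that the ranking is uncertain. They do not re-centre the estimate.

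**4. Absolute scale**

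With a common RR of 0.85 and baseline rates of 10, 20 and 40, the events averted are 10 × 0.15 = 1.5, 20 × 0.15 = 3 and 40 × 0.15 = 6. A group can truly gain more with no difference in relative effect.

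**5. Whether the remedy works**

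With equal effects, a 5% heterogeneity test declares a difference in about 5% of replicates. Empirical-Bayes shrinkage (K = 10, 1,000 events per stratum) moves the lowest RR from 0.771 to 0.829, against a truth of 0.85.

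**The case against.** **No selection rule is written.** A reader might infer that targets are chosen by taking the largest stratum estimate, so that a target is always returned, or by screening strata at p < 0.05. The article supports neither. It says benefits are compared and coverage could be more beneficial, and the tuning sentence concerns the mix of socioeconomic change and coverage. This stands, and the simulations show only what happens to whichever group looks best.

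**A best group may be real.** A reader might also infer that naming a group is wrong whenever relative effects are equal. It is not. Scenarios are also compared on averted cases and deaths, which depend on baseline burden (check 4). This stands too. Noise in the relative effect still enters the absolute figures.

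**The data are very large.** The introduction reports 835.791 notified AIDS cases (point as thousands separator), and the cohort holds about 114 million registrations. Linked events are not given, but for full-cohort incidence the distortion is probably small. The objection is weaker for RDD within a bandwidth, for FHS limited to municipalities with 0–10% or 90–100% coverage, and for mortality and case fatality.

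**Uncertainty is propagated.** It is, and the predictive intervals can show that groups are indistinguishable. They do not remove the bias (check 3).

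**The article is condensed.** A fuller analysis plan may contain heterogeneity analyses, and stratified estimates do not exclude them. The point is therefore not that something is missing. The article states a subgroup method and its downstream use, and a better method is available at low cost.

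**Conclusion.** The point holds in a limited form. Stratum-specific effects from separate fits feed the comparison of target groups, with no described estimate of how far effects differ and no pooling. The relative effect of a group that looks best partly by chance will be overstated in the projections.

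The size cannot be fixed from the article. Under a common IRR of 0.90 and 22 strata it ranges from about 2.7-fold at 1,000 total events to about 1.2-fold at 100,000. Those figures assume equal-sized levels, half the person-time exposed, and that the stratum with the lowest IRR is the one looked at. If effects truly differ, or if baseline burden drives the comparison, the overstatement is smaller. The practical weight lies in the sparse analyses.

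**What to change.** **Aim 2, Steps 2 and 4.** Add exposure-by-subpopulation terms to the regression models. For RDD and PSM, derive a between-stratum heterogeneity estimate from the stratified results. Report it with its confidence interval, and obtain partially pooled (hierarchical or empirical-Bayes) stratum effects.

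**Aim 3.** Use the pooled effects with their covariance as model inputs. From the Monte Carlo draws already planned, report intervals for the differences in benefit between target groups, and the probability that each group is the most beneficial. Where heterogeneity is not supported, pooling pulls the strata towards a common effect, and groups then differ mainly through baseline burden.

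**Cost.** Modest extra modelling on data and draws already planned. Subgroup contrasts will be smaller, and fewer groups will stand out.
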